### Statistical analysis

#### Primary outcome parameter and other MRI-derived parameters

TBSS analysis will be performed as previously described [61]. In summary, group comparisons will be performed with FMRIB Software Library’s Randomise tool using a general linear univariate model, [62] with family-wise error correction for multiple testing using threshold-free cluster enhancement with a significance level of *p* < 0.05 [63]. Group comparisons for volumetric analyses will be performed with ANOVA, with false discovery rate to correct for multiple testing. In all analyses GA at birth, postmenstrual age at time of MRI, birth weight Z-score and days of ventilation will be entered as covariates. These analyses have been used in several other observational and intervention studies conducted in the UMC Utrecht and other research groups, in preterm infants at TEA (mean and median GA of 28.7 weeks), [52, 64] healthy and asphyxiated full term infants, [65, 66] as well as children at school age (7.5–8.5 years and 12 years of age) [67–69].

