### Outcome measures

#### Primary outcome

The primary outcome parameter in this study is integrity of white matter tracts throughout the brain, measured as FA assessed with DTI magnetic resonance imaging (MRI) at TEA. DTI detects the direction of diffusion of water molecules, which is influenced by the process of increasing myelination. Many studies have shown that FA - a measure of degree of diffusion in one direction - and tractography - a reconstruction of tracts using FA - are predictive of long-term neurodevelopmental outcome [52]. DTI images will be analysed using Tract-Based Spatial Statistics (TBSS), [53] part of the FMRIB Software Library [54]. TBSS is a voxelwise statistical method in which all infants FA data will be projected onto a mean FA tract skeleton and will be cross-subject analysed. TBSS analysis is sensitive as an imaging biomarker in the preterm population, [55] and can be used as a suitable biomarker of disease and treatment effects in children born very preterm [52, 55, 56].

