### Sample size calculation

The sample size needed for TBSS analyses has been estimated based on previous simulations of the sensitivity of TBSS for detecting treatment effects, as reported by Ball et al., who recruited infants with GA < 36 weeks who underwent successful DTI at TEA (baseline characteristics: median GA [range] 28 + 6 [23 + 4–35 + 2], median birthweight [range] 1130 g [630–3710 g]) [55]. The likelihood of TBSS detecting an effect of the intervention on the FA will depend on the overall FA increase and its distribution around the mean FA increase. The effect of the current intervention on FA is unknown. We hypothesize that the increase in FA in the intervention group will be moderate, in the order of 5%. TBSS analyses the relation between different parameters (e.g., GA, sex, intervention group) and the FA of voxels of the white matter skeleton (i.e., the inter-subject aligned centre of white matter tracts). Based on the simulations in neonates reported by Ball et al., in order to detect an estimated increase in FA of 5% in approximately 50% of the TBSS skeletal voxels 35 infants per intervention group are required [55]. They showed that TBSS can detect clinically relevant global differences in FA, even in small groups and can therefore be used as a powerful biomarker of white matter development [55]. In a recent study comparing the effects of high vs. lower breast milk exposure in 20 vs. 27 preterm infants group wise differences in brain connectivity at TEA were shown with TBSS [61]. Based on these results we assume this whole-brain DTI analysis technique is sensitive to the effects of our intervention with 35 evaluable infants per intervention group. In total 70 evaluable infants will be needed. To account for potential drop-outs and non-evaluable infants, the target population should consist of 88 randomised infants. This number includes allocated twins/multiple births.

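### The trial is sized on an FA increase of about 5%, but the only primary analysis stated is a voxelwise corrected test, which alone gives no quantity to compare with 5%

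*Protocol article*

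**What the plan says.** All references are to the protocol article.

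- **Primary outcome** defines the endpoint: "The primary outcome parameter in this study is integrity of white matter tracts throughout the brain", measured as FA on DTI at term equivalent age. It describes the method so: "TBSS is a voxelwise statistical method in which all infants FA data will be projected onto a mean FA tract skeleton". No single summary value of FA per infant is named.
- **Sample size calculation** gives the hypothesis: "We hypothesize that the increase in FA in the intervention group will be moderate, in the order of 5" per cent. The number of infants follows from a cited simulation study: "to detect an estimated increase in FA of 5% in approximately 50% of the TBSS skeletal voxels 35 infants per intervention group are required". The same section says that the chance of detection "will depend on the overall FA increase and its distribution around the mean FA increase". It gives no value for that spread.
- **Primary outcome parameter and other MRI-derived parameters** describes the test in summary form and refers to a cited study for the method. It is a general linear model in FSL Randomise, "with family-wise error correction for multiple testing using threshold-free cluster enhancement with a significance level of" p < 0.05. The covariates are gestational age at birth, postmenstrual age at MRI, birth weight Z-score and days of ventilation.
- **The section on safety, exploratory and non-MRI outcomes** defers statistical details to an analysis plan that is not shown. It also sets the analysis population for the primary outcome.

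**The concern.** The sample size rests on two quantities: a magnitude (5%) and an extent (about 50% of skeleton voxels). The stated test reports on neither. Its output is a map of corrected p-values, and the article does not say how that map is to be read against the 5% or the 50%.

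This matters whichever way the trial turns out. If a few voxels survive correction, the result shows an effect somewhere, while the endpoint is described for tracts over the whole brain. If none survive, readers will ask whether a 5% gain has been ruled out, and the test alone cannot tell them. If a global summary is chosen only after the map has been seen, that choice is open to the charge of being data-driven.

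**Working it through.** **1. The plan's own figures.** The 35 per group comes from a cited simulation study. The article gives no SD of FA, no power and no sidedness, so no closed formula reproduces it. The step from 70 evaluable to 88 randomised fits an unstated loss of 20%: 70 / (1 − 0.20) = 87.5, rounded up to 88.

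**2. What the stated test can conclude.**
- *Significant map.* Rejection at family-wise corrected p < 0.05 is rejection of zero effect at the surviving voxels. It puts no size on the effect.
- *Non-significant voxel.* Suppose the sizing sentence means that a uniform 5% increase is detected in about half of the voxels. Then a voxel with a true 5% gain is missed about 1 − 0.50 = 50% of the time, so non-significance there does not exclude 5%. A truly global effect could also look regional.
- *Non-significant map.* The 50% is an average over voxels. Voxels in one trial share the same infants, and the article gives no probability that the whole map is empty when 5% is true. So no error rate attaches to reading an empty map as excluding 5%.

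**3. What a supporting estimate could show.** Take mean FA over the skeleton for each infant, with n = 35 per group and two-sided alpha 0.05. Express the SD as a percentage of mean FA. The SD is an **assumption**, because the documents give none.

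- CI half-width = 1.96 × SD × √(2/35) = 1.96 × SD × 0.239
- Power for 5% = Φ(5 / (SD × 0.239) − 1.96)

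| Assumed SD (% of mean FA) | 95% CI half-width (percentage points) | Power for 5% |
|---|---|---|
| 5 | 2.3 | 99% |
| 7.5 | 3.5 | 80% |
| 10 | 4.7 | 55% |
| 12 | 5.6 | 41% |
| 15 | 7.0 | 29% |

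The half-width equals 5 points at SD = 5 / (1.96 × 0.239) ≈ 10.7%. Below that SD, an estimate near zero would exclude 5%. Above it, it would not.

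The table treats infants as independent. Under Treatment allocation and blinding, twins and multiples share an allocation, and the sample size section counts them in the 88, so the true precision may be lower. Covariate adjustment may offset some of this.

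**4. A second reading of the sizing sentence.** It could mean that the 5% gain is present in only about half of the voxels. With no effect elsewhere, the skeleton mean would then rise by roughly 0.5 × 5% + 0.5 × 0% = 2.5%. The references to an overall increase and to global differences favour the first reading, but the plan should say which is meant before the mean is compared with 5%.

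**The case against.** **The article is a summary.** It refers to a cited study for the TBSS method and to an analysis plan for details. Effect estimates and intervals beside a voxel map are often specified there. The deferral sentence stands under a heading for non-MRI outcomes, but the same section also fixes the primary analysis population, so it may cover MRI too. This stands: absence from the article does not prove absence from the plan.

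**Design and analysis use the same method.** The trial is sized on simulations of TBSS sensitivity and analysed with TBSS. Sizing on the proportion of voxels detected and then testing voxelwise is not an error. This also stands.

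**Stronger conclusions that a reader might infer, and that the documents do not support:**
- *That the trial cannot confirm or exclude 5% at all.* The model gives a group coefficient at every voxel, and a skeleton mean can be computed from the same images. The gap is in what is pre-specified.
- *That one surviving voxel makes the trial positive, or would be claimed as a brain-wide effect.* The article states a significance level. It writes no such success rule.
- *That a test of mean FA is sure to have high power.* If each voxel is taken to have 50% power at a fixed threshold z, the scalar test has power Φ(z − 1.96): 85% at z = 3 and 98% at z = 4, but 71% at z = 2.5 and 52% at z = 2. Threshold-free cluster enhancement uses no fixed voxel z, so none of these can be claimed as a lower bound.

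What remains is that the article fixes the hypothesis, the basis of the sample size and the test, and that the test alone does not speak to the hypothesis.

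**Conclusion.** The point holds as a gap in pre-specification. The stated primary test gives no quantity to set against the 5% on which the trial was sized, so a null or partial map could not be interpreted against that 5%. The size of the gain from a supporting estimate depends on an SD that the documents do not give. At an SD of about 7.5% of mean FA or less, 35 per group would usually separate 0% from 5%. At about 10.7% or more, it would not. Both statements assume independent infants and the global reading of the sizing sentence. No stated figure is shown to be wrong, and TBSS remains a reasonable primary method. If the unseen analysis plan already contains such an estimate, the point is met.

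**What to change.** Keep TBSS as the primary localising analysis. In the analysis plan, before unblinding:

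1. Add mean FA over the TBSS skeleton as a supporting estimate: an adjusted between-group difference with 95% CI, in FA units and as a percentage of the control mean, read against the 5% hypothesis.
2. Adjust for gestational age at birth, postmenstrual age at MRI, birth weight Z-score and sex. Sex is the stratification factor and is absent from the stated covariate list. Account for twins and multiples by mother. Do not describe days of ventilation as a baseline covariate, since it accrues after birth and during the intervention.
3. Report the percentage of skeleton voxels that are significant, beside the planned 50%, and state which reading of the sizing sentence is meant.
4. Describe an effect as brain-wide only if the mean difference supports it.
5. Claim no power for the supporting estimate unless an SD is supplied.

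**Cost.** Slight extra analysis, with no new infants or scans, because the mean comes from the same skeletonised images. A focal effect is diluted in the mean, which is why the TBSS map stays.

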### Treatment allocation and blinding

After eligibility has been assessed and informed consent has been obtained the infant will be enrolled in the study. To randomise an infant to the study, investigators will log in to the electronic Case Report Form (eCRF) and follow the prompts to input infant data. Only investigators specifically trained to perform randomisation will have access to the eCRF. Based on the order in which infants enter the study and stratified by sex, the infant will be assigned a randomisation number by the eCRF system. The infant will receive the product with the code corresponding to his/her randomisation number. Twins and multiple births will be allocated to the same study group. Investigators, all site staff including medical and nursing staff and supporting staff who prepare the infant feedings, and parents will be unaware of treatment allocation.

The randomisation sequence will be generated using the PLAN procedure of SAS statistical software (Enterprise Guide version 4.3 or higher) by a statistician from Danone Nutricia Research who has no further involvement in the conduct of the trial. The permuted block randomisation will be stratified by sex (boys, girls) with a 1:1 allocation ratio of test and control product. The block size or sizes and whether the block size(s) will be fixed or randomly varied will be decided by and known only to the statistician. The packaging of the test and control products will be identical in appearance. The study product for each infant will be labelled using a unique random number according to the randomisation schedule. These random numbers will have been linked (via a code) beforehand to either test or control product. Which numbers correspond to which treatment will only be known to the supplies manager at Danone Nutricia Research.

The randomisation code will be broken after analysis of the primary outcome and other outcomes collected until TEA. Assessors, parents, hospital staff and all those involved in the conduct and/or decision making of the follow-up phase will remain blinded to study product allocation until follow-up database lock after the last infant has completed the study (24 months corrected age). In the case of a medical emergency that requires preliminary unblinding of study product, unblinding in the eCRF or with sealed unblinding envelopes stored at the UMC Utrecht will be possible.

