### Supplementation

Study product supplementation will start between 48 and 72 h after birth or, if the infant is clinically unstable as soon as possible thereafter, and will continue until 36 weeks postmenstrual age. If the infant is discharged home or fully breastfed before 36 weeks postmenstrual age supplementation will be stopped. Study product Part A will be administered enterally once per day as a single daily dose not supplemented to feeding or medication. The dosage of *B. breve* will depend on birth weight: Infants with a birth weight ≥ 1000 g will receive 3 × 10^9^ colony-forming units (cfu) per day; Infants with a birth weight < 1000 g will receive 1.5 × 10^9^ cfu per day, to be increased to 3 × 10^9^ cfu per day when they have reached enteral feeding intakes of 50 ml/kg/day. Study product Part B will be administered enterally supplemented to the regular milk feed (breast milk or preterm formula, depending on parents’ choice). Dosage will be increased in a stepwise fashion. Based on the infant’s weight, daily intake of enteral feeding and the desired (maximum) osmolarity of the feeding, a supplementation schema was created, starting with a minimum dosage of 0.05 g/day L-glutamine and 0.1 g/day scGOS/lcFOS and aiming for a final dose of 0.3 g/kg/day L-glutamine and 0.6 g/kg/day scGOS/lcFOS when the infant receives full enteral feeding (120 ml/kg/day for 1 day). The final dosages of L-glutamine and scGOS/lcFOS were based on the GEEF study [45] and CARROT study [51], respectively, in which supplementation was well tolerated.

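### Milk feed, which the protocol's own cited evidence links to TBSS differences, is missing from the covariates fixed for every MRI analysis

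*Protocol article*

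**What the plan says.** All places are in the protocol article.

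- **Sample size calculation.** The planned size is stated as "skeletal voxels 35 infants per intervention group are required". In support, the section cites a comparison of "high vs. lower breast milk exposure in 20 vs. 27 preterm infants group wise differences in brain connectivity at TEA were shown with TBSS" and continues: "Based on these results we assume this whole-brain DTI analysis technique is sensitive to the effects of our intervention with 35 evaluable infants". The analysis section gives the same reference as its model for the TBSS analysis.
- **Supplementation.** The regular milk feed is "breast milk or preterm formula, depending on parents’ choice".
- **Treatment allocation and blinding.** "The permuted block randomisation will be stratified by sex (boys, girls) with a 1:1 allocation ratio of test and control product". Feed is not a stratification factor.
- **Primary outcome parameter and other MRI-derived parameters.** "In all analyses GA at birth, postmenstrual age at time of MRI, birth weight Z-score and days of ventilation will be entered as covariates". None of the four concerns feed.
- **Data collection.** Enteral and parenteral feeding characteristics and cumulative intake are recorded. Feed choice at enrolment is not listed as a separate item.
- **Safety, exploratory and non-MRI secondary parameters.** Under this heading the protocol says that baseline characteristics will be looked at when the analysis starts and that important confounders will be added as covariates. Its example is antibiotic exposure; feed is not named.

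**The concern.** The protocol relies on a breast-milk contrast being visible on TBSS in groups of 20 and 27, both smaller than its own 35. It then fixes a covariate list for all MRI analyses that leaves milk feed out. If feed is related to fractional anisotropy (FA), two things follow in a trial of about 70 evaluable infants:

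- Variation in FA due to feed stays in the voxelwise residual, so the comparison is less precise than it need be.
- If the arms happen to differ in feed, part of the observed contrast reflects feed, and the fixed model makes no correction.

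The clause on confounders is a weak remedy. It sits under a heading for outcomes not derived from MRI, names no feed variable, and leaves the choice until the data have been inspected. If feed were added only when an imbalance was seen, the precision available in balanced data would also be lost.

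**Working it through.** **The plan's own figure.** The 35 per group is read from published TBSS simulations. The article gives no SD and no power, so no closed formula reproduces it. The step from 70 to 88 follows from an assumed 20% loss: 70 / (1 − 0.20) = 87.5, rounded up to 88. The dispute is not about these figures.

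**Inputs.** From the article: 35 evaluable infants per arm, and 20 vs 27 in the cited study. Assumed, because the article does not give them: the share p of infants on breast milk (0.3 to 0.7), the standardised effect d of feed on FA (0.3, 0.5 and 0.83 SD), a single two-sided test at 0.05, and 80% power for the feed-adjusted analysis. A single test simplifies the voxelwise, family-wise-corrected analysis, so the results are illustrative.

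The upper value of d is what 20 vs 27 would detect with 80% power in a single test: (1.960 + 0.842) × sqrt(1/20 + 1/27) = 0.83. It is a benchmark, not an effect reported in the article.

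**1. Chance imbalance in feed.** For independent infants the SD of the arm difference in proportion is sqrt(2p(1 − p)/35):

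- p = 0.3 or 0.7: sqrt(2 × 0.21/35) = 0.110
- p = 0.5: sqrt(2 × 0.25/35) = 0.120

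Exact binomial probabilities:

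| Assumed share p | Gap ≥ 10 points | Gap ≥ 20 points |
|---|---|---|
| 0.3 or 0.7 | 36.1% | 8.9% |
| 0.5 | 40.3% | 12.0% |

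With 35 per arm, a gap of at least 10 points means at least 4 infants (4/35 = 11.4%). Multiples are allocated to the same group. If they also share a feed, imbalance becomes more likely, but the article does not give the number of multiples, so this is not quantified.

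**2. What a gap does to the contrast.** The shift equals gap × d. For a 20-point gap it is 0.2 × 0.3 = 0.06 SD up to 0.2 × 0.83 = 0.17 SD. For comparison, 35 per arm detects (1.960 + 0.842) × sqrt(2/35) = 0.67 SD with 80% power in a single test.

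**3. Precision lost by omission.** Leaving out a binary factor multiplies the residual variance by v = 1 + p(1 − p)d². Power becomes Φ(2.802/√v − 1.960).

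| d (SD) | v for p = 0.3 or 0.7 | v for p = 0.5 | Power, from 80% |
|---|---|---|---|
| 0.3 | 1.019 | 1.022 | 79.3% to 79.1% |
| 0.5 | 1.052 | 1.062 | 78.0% to 77.6% |
| 0.83 | 1.145 | 1.172 | 74.5% to 73.5% |

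Since v is also the ratio of sample sizes, omission equals needing about 2%, 5–6% and 15–17% more infants. Steps 2 and 3 are two views of the same loss, because the unadjusted standard error already allows for chance imbalance. They should not be added together.

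**The case against.** **Randomisation takes care of it.** Feed is balanced in expectation, and chance imbalance is part of the test's error rate. A reader might infer that the omission biases the trial or makes its primary test invalid. The documents do not support that. What remains is precision and the absence of adjustment in the trial actually obtained.

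**The cited study is thin evidence.** The article gives no effect size, no FA figure and no adjustment details for it. A reader might take it to show that breast milk by itself changes FA by a known amount; the article reports only group differences between exposure levels. The contrast there is degree of exposure, whereas feed choice at enrolment is a proxy whose relation to FA the documents do not establish. This stands and limits the expected gain.

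**The stopping clause.** A reader might infer that breast-milk feeding also cuts exposure to the product, from "If the infant is discharged home or fully breastfed before 36 weeks postmenstrual age supplementation will be stopped". The same section has Part B added to breast milk as well as to formula. The clause most plausibly refers to feeding at the breast, not to type of milk. It also concerns an event after randomisation, which an enrolment variable would not capture. The point does not rest on it.

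**The general clause and the unseen SAP may cover it.** The clause on confounders is followed in the same paragraph by the primary analysis population, so it may apply to the primary outcome. It is not expressly conditional on imbalance. The code is broken only after the primary analysis, so covariates would be chosen without knowing which arm is active. The SAP may also name feed. This softens the point but does not remove it: the protocol states a fixed list for all MRI analyses, and the clause leaves the choice of any addition until the data are in hand.

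**Conclusion.** The point holds as a modest, inexpensive improvement. The protocol uses a breast-milk contrast as evidence that TBSS is sensitive in small groups, and then fixes an MRI model without milk feed. The comparison remains unbiased and the test valid.

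The loss is about 1 to 6 percentage points from an assumed 80% power, for assumed feed effects of 0.3 to 0.83 SD. A feed gap of at least 10 points between arms would go unadjusted in roughly 36–40% of trials of this size. These figures rest on an assumed feed share of 30–70%, independent infants and a single-test simplification. Only the group sizes come from the article. At the lower feed effects the loss is slight.

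**What to change.** In the section on the primary outcome and other MRI-derived parameters, add a fifth covariate to the TBSS and volumetric models: milk type or parents' feed choice (breast milk vs preterm formula), recorded at or before the first study product. Prespecify it, with its coding, before unblinding, and enter it whether or not the arms turn out balanced.

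Do not adjust the primary comparison for cumulative milk intake after randomisation. The product could affect that intake, for example through feeding tolerance, and adjusting for it could remove part of the effect or introduce bias.

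**Cost.** One residual degree of freedom: 70 infants less intercept, group and four covariates leaves 64, and 63 with feed added. Feeding characteristics are already collected, so the only new item is the choice or milk type at that time point. The gain will be small if this variable predicts FA only weakly.
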